**List 1: Added Versus Natural Sugar**
This week I feel motivated to...spend time watching TV.do the vacuuming in my home.spend time chatting with my friends on the web.pick a fight with my partner.rinse my nose with salt water daily.cut my daily intake of added sugar (sensitive item).
**List 2: Sugar-Sweetened Beverages**
This week I feel unmotivated to...wash my hands frequently.spend time watching movies.clean the toilets in my home.smoke marijuana.clip my toenails.reduce the amount of sugar-sweetened beverages I drink (sensitive item).
**List 3: Fresh Fruit**
This week I feel motivated to...open up a new savings plan at the bank.practice playing a musical instrument.watch a pornographic movie.do some shopping on the web.clean kitchen counters after use.eat fresh fruit daily (sensitive item).
**List 4: Food Labels**
This week I feel motivated to...watch a new TV series.practice meditation daily.have alcoholic drinks on at least 3 evenings.catch up on last week’s work.clean all floor surfaces.check food labels for sugar content (sensitive item).
**List 5: Teaspoons of Sugar**
This week I feel unmotivated to...clean my dishes after use.spend time on the internet.try learning a new language.play a prank on my partner.visit a car sales website.count how many teaspoons of added sugar I eat each day (sensitive item).
**List 6: Home Cooking**
This week I feel unmotivated to...stock up on household supplies for a month.spend time gardening by myself.plan my next holiday.take a web-based course.go out with my friends.cook with fresh, whole foods (sensitive item).

#### Secondary Outcome Measure

We will measure participant engagement as a secondary outcome. At the end of the study, we will offer participants randomized to the placebo videos the choice to watch the sugar-intervention video or end the survey. The Gorilla platform will record this response. If the *Watch Video* button is clicked, Gorilla will randomize the participant to 1 of the 3 sugar videos and record the time (in milliseconds) from the start of the video until the participant clicks the *Finish* button or until the end of the video, whichever comes first. These data will be used to assess objective 3.

### Participant Timeline

Participants are expected to finish the trial (watch the video, answer the survey questions, and complete the list experiment) in 10 minutes. The complete schedule of enrollment, interventions, and assessments is shown in Figure 3.

**Figure 3 figure3:**
[figure not shown]
Schedule of enrollment, interventions, and assessments.

### Recruitment

We will use the Prolific platform to recruit the study participants. The user must create an account on Prolific and provide their personal information. Participants must agree with Prolific’s data privacy terms and conditions. Prolific will assign each participant a unique, anonymized ID. The study investigators will also create a Prolific account. We will instruct the Prolific platform on how many participants need to be recruited, and it will filter out all participants who do not meet the eligibility criteria. Participant entry into our study will happen on a *first-come, first -served* basis until the recruitment number (sample size) is reached. We will compensate the participants an equivalent of £1 (US $1.4) for the expected 10-minute completion time.

### Assignment of Interventions: Allocation

#### Sequence Generation

The Gorilla platform is specifically designed to host and implement web-based experimental studies. Gorilla will randomly allocate participants to the five trial arms.

#### Concealment Mechanism

The Gorilla platform uses a web-based randomization algorithm that is unknown to us.

#### Implementation

The Gorilla platform will complete the implementation.

### Assignment of Interventions: Blinding

#### Who Will Be Blinded?

As Prolific handles the interaction between the study investigators and participants, the participants will be completely anonymous to the study investigators. Only the participant’s unique, anonymized ID will be used to manage the linking between the Prolific and Gorilla platforms. The outcome measures will be self-reported and submitted anonymously. The study investigators and those involved in the data analyses and statistics will be blinded to the group allocation.

### Data Collection and Management

#### Plans for Assessment and Collection of Outcomes

Data will be collected on the Gorilla platform, where participants can submit data by clicking on the response buttons. We expect to collect data over a 1- to 2-week period.

#### Plans to Promote Participant Retention and Complete Follow-up

The expected completion time for the experiment is 10 minutes. Participants will be automatically timed out of Gorilla if they take longer than 45 minutes to complete the survey. The time-out is to ensure that participants do not clog up the system with incomplete surveys. As the participants will be anonymous to us, there is no way to initiate follow-up in the maximum 45-minute time limit.

### Data Management

All trial participants will be assigned a unique, anonymized string ID. The ID will be used on the Gorilla platform and linked to the participants’ responses. Gorilla will store the trial data on its cloud platform hosted on Microsoft Azure in the Republic of Ireland. The Gorilla database is encrypted using industry-standard cryptography. The study investigators own the research data collected using Gorilla and have complete control over it. The study investigators can generate and access the completely anonymized data from the Gorilla platform. The data will be downloaded and stored safely for statistical analysis on a computing system maintained by Heidelberg University in Germany.

### Confidentiality

Participants, who are completely anonymous to us, will have no identifying information associated with their unique IDs. We will inform participants that if they email the study investigators then their names could be revealed to us. The study investigators will keep this information confidential.

### Statistical Methods

#### Statistical Methods for Primary and Secondary Outcomes

For the descriptive statistics, we will obtain means and SDs of age, sex, country of residence, and education status variables. We will use an analysis of variance to estimate pairwise differences in means between the sugar-intervention videos, content placebo video, and placebo video. We will use the Tukey range method to create confidence intervals for all pairwise differences between the means while controlling for the family error rate. Within each trial arm, we will estimate the prevalence of behavioral intent as the difference between the treatment and control list for each list experiment. From these estimates, we will obtain the differences in means between trial arms. This approach is analogous to a difference-in-difference analysis, which we will implement by specifying the main and interaction terms in an ordinary least squares (OLS) regression model. The OLS equation for each list experiment is given as follows:

y = b_0_ + b_1_*VideoArm* + b_2_*TreatList* + b_3_*VideoArm* × *TreatList*

where y is the number of statements in the list that the participant agreed with, *VideoArm* indicates the arm to which the participant was assigned, and *TreatList* indicates if the participant was assigned to the treatment list within that arm. We will calculate standard errors, 95% CIs, and *P* values for linear combinations of coefficients from the OLS model. We will use R statistical software to perform the analysis.

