## Methods

### Trial Design

This study consists of a parallel group RCT. Participants will be randomized to 1 of 5 arms: either the same sugar-intervention video narrated by a preadolescent daughter (arm 1: low social authority), the daughter’s mother (arm 2: equivalent social authority), or a family physician (arm 3: high social authority), or a content placebo video with a health message about tanning and sunscreen (arm 4: no sugar message), or a placebo video about earthquakes (arm 5: no sugar or health message). We will randomize the participants in a 1:1:1:1:1 ratio to the trial arms. Participants will watch 1 video once from start to finish.

Nested in each of the five trial arms is a list experiment. For each list experiment, participants will be randomized at a 1:1 ratio to a control or treatment group. The control group will receive a list of 5 items about behavioral intent (unrelated to sugar consumption). The treatment group will receive the same 5 items and a sensitive item about behavioral intent to reduce sugar intake. We will use the list experiment to reduce social desirability bias, as participants may already be primed to answer favorably to questions about sugar consumption.

At the end of the study, participants assigned to the content placebo (*arm 4*) or placebo (*arm 5*) will be given a choice to watch the video intervention. Their choices will be recorded. Participants who choose to watch will be randomized at a 1:1:1 ratio to the sugar video narrated by the daughter, mother, or physician. The complete trial flowchart is presented in Figure 1.

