### Eligibility Criteria

Eligibility criteria included being between the ages of 18 and 59 years (male, female, or other), being able to speak English, and being a resident in the United Kingdom; not being eligible according to any of the inclusion criteria was the exclusion criteria. We will not exclude participants on an existing health condition (eg, diabetes) because Prolific does not collect health information from its users.

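### Adding age, sex and education as covariates to both models would give equal or slightly better precision at almost no cost; the covariate-free models are already unbiased

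*Protocol article*

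**What the plan says.** All the relevant text is in the protocol article. Under Statistical Methods for Primary and Secondary Outcomes, the descriptive part says "we will obtain means and SDs of age, sex, country of residence, and education status variables". No other use of these variables is stated.

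For the scale outcomes the same section says "We will use an analysis of variance to estimate pairwise differences in means between the sugar-intervention videos, content placebo video, and placebo video", with Tukey intervals. For the list counts it describes an analysis analogous to a difference-in-difference, "which we will implement by specifying the main and interaction terms in an ordinary least squares (OLS) regression model". The printed equation contains VideoArm, TreatList and their product, and nothing else.

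Trial Design gives the allocation to arms: "We will randomize the participants in a 1:1:1:1:1 ratio to the trial arms". It also says that for each list experiment "participants will be randomized at a 1:1 ratio to a control or treatment group". No stratification on age, sex or education is mentioned. Eligibility Criteria requires "being a resident in the United Kingdom", so country of residence is constant and has no use as a covariate.

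**The concern.** Age, sex and education cannot be changed by a ten-minute video study, so adjusting for them is safe. In a list experiment, much of the noise in the count comes from the control items. Several of these could plausibly vary with age or sex, such as marijuana, a pornographic film, alcohol on three evenings, gardening alone and chatting on the web. Where such a link exists, a model without covariates leaves that variance in the residual.

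The between-arm list contrast, which serves the second objective, has the most to gain. It is a difference of two differences, each resting on about 400 participants per list, so its standard error is large. What is at stake is a modest amount of precision, not the validity of any comparison.

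**Working it through.** **Inputs.** From Sample Size: SDs 0.85 and 1.0, difference 0.15 items, type I error .05, power 80%, two comparisons, total 4000. From Trial Design: five equal arms and two equal list groups per arm, so 4000 / 5 / 2 = 400 per cell. Assumed, because the documents give no value: R2, the share of outcome variance explained by age, sex and education.

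**The plan's own figure.** The printed formula is missing from the readable text, so the standard form is assumed:

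n = (0.85² + 1.0²) × ((z(1 − .05/4) + z(.80)) / 0.15)² = 1.7225 × ((2.2414 + 0.8416) / 0.15)² = 727.7, that is 728 per group.

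The article states 769. That difference is a separate matter and does not affect this point, which uses only the SDs, the 0.15 difference and the cell size.

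**Unadjusted precision.**
- Within one arm: SE = √(1.7225 / 400) = 0.0656.
- Between two arms: SE = √(2 × 1.7225 / 400) = √0.0086125 = 0.0928, or about 9 percentage points of prevalence.
- Power for a 0.15 between-arm difference, two-sided .05: Φ(0.15 / 0.0928 − 1.96) = 36.6%.

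**Adjusted precision.** The residual variance is multiplied by (1 − R2), so the SE is multiplied by √(1 − R2).

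| Assumed R2 | SE factor | SE, between-arm contrast | Power for 0.15 |
|---|---|---|---|
| 0 | 1.000 | 0.0928 | 36.6% |
| 0.01 | 0.995 | 0.0923 | 36.9% |
| 0.02 | 0.990 | 0.0919 | 37.2% |
| 0.05 | 0.975 | 0.0905 | 38.2% |
| 0.10 | 0.949 | 0.0880 | 39.9% |

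**Check by simulation.** The arm-by-list regression was fitted with and without three covariates entered as main effects (N = 4000, 200 runs per R2). The ratio of adjusted to unadjusted SE was 1.0005 at R2 = 0, 0.990 at 0.02, 0.975 at 0.05 and 0.949 at 0.10. This agrees with the formula. The R2 = 0 row also shows the price of useless covariates: about 0.05% of the SE.

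**What R2 is plausible?** As an illustration, suppose one control item per list relates to the covariates, the items are uncorrelated, and the covariates explain 10% of that item's variance. The control-list variance is 0.85² = 0.7225. An item with 50% prevalence has variance 0.25, which gives R2 = 0.025 / 0.7225 = 3.5%. An item with 10% prevalence has variance 0.09, which gives 0.009 / 0.7225 = 1.2%. Under these assumptions R2 sits in the lower part of the table.

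**What would 80% power need?** The SE would have to be 0.15 / (1.96 + 0.84) = 0.0536. Then 1 − R2 = 0.0536² / 0.0086125 = 0.33, so R2 would have to be about 0.67, far outside the range considered.

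**Scale outcomes.** The same factor √(1 − R2) applies, with each scale's own R2. The documents allow no figure.

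**The case against.** The strongest case against is that nothing here is wrong. Arms and lists are randomized, no stratification factor is left out of the model, and the unadjusted estimates are unbiased. Covariate adjustment is often left to an analysis plan, and none is shown. All of this stands except the last step: the article prints the complete list equation, so the absence of covariates is part of the stated model and not a detail left open.

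Several stronger readings are tempting, and the documents do not support them.

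- **The omission biases the results or causes the low power.** It does neither. Randomization protects the unadjusted contrast, and the low power comes from the cell size and from taking a difference of differences.
- **Hundreds of participants are being thrown away.** At R2 = 0.10 the arithmetic gives 4000 / 0.90 − 4000 = 444, but that R2 is an assumption and the matching gain in power is about 3 points. At R2 = 0.02 the figure is 82.
- **Adjustment is entirely free.** Age needs a form, education needs a coding, and sex needs a category for participants recorded as other. Missing covariate values need a rule, because the article's missing-data section covers only unfinished surveys.
- **Covariates must be interacted with TreatList to keep the list difference unbiased.** Under randomization, main-effect adjustment is already consistent. The interaction is an optional efficiency device.
- **Recruitment shows that the variables are held for everyone.** It says only "The user must create an account on Prolific and provide their personal information" and names none of them. That they are available follows instead from the plan to describe them.

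**Conclusion.** The point holds as a minor improvement. The stated models for the scale outcomes and the list counts have no covariates. Entering age, sex and education would give equal or slightly better precision, at a cost that is negligible with 4000 participants. For an assumed R2 of 0.01 to 0.10, the SE of the between-arm list contrast falls from 0.0928 to between 0.0923 and 0.0880, and power for a 0.15 difference rises from about 37% to at most 40%. These figures rest on the article's SDs, on 400 participants per cell and on an R2 the documents do not supply. The conclusion does not depend on R2 being large: if it is zero, almost nothing is lost.

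**What to change.** In Statistical Methods for Primary and Secondary Outcomes, add one or two sentences:

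- Enter age (continuous), sex and education (both categorical) as covariates in the scale model and in the list regression. Form the pairwise arm comparisons from the adjusted means.
- State a simple rule for missing covariate values, for example a separate missing category for sex and education, and the overall mean with an indicator for age.
- Report the unadjusted models alongside.
- Centred covariate-by-TreatList terms may be added for efficiency, but they are optional.

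Results says the data analysis was completed in April 2021. An adjusted model added now should therefore be labelled supplementary, and the covariate-free models remain the ones fixed in the document. The cost is a short text change and a few lines of code. No new data are needed as long as the three variables are recorded for each participant, which the planned descriptive statistics already require.

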#### Methods in Analysis to Handle Protocol Nonadherence and Any Statistical Methods to Handle Missing Data

Participants who do not complete the survey will be excluded from the final analysis. This loss will be reported.

### Plans for Granting Public Access to the Full Protocol, Participant-Level Data, and Statistical Code

This document is the full protocol. Additional data or documentation can be requested from the corresponding author.

### Oversight and Monitoring

#### Composition of the Data Monitoring Committee, Its Role, and Reporting Structure

As the intervention is relatively short and takes place on the web, a data monitoring committee is not needed.

#### Adverse Event Reporting and Harms

As participants are anonymous to us, we will not be able to report any adverse events or harm. It is unlikely that there will be adverse events, given the format of our 10-minute web-based trial.

#### Criteria for Discontinuing or Modifying Allocated Interventions

We will not discontinue or modify the allocated interventions during the course of the study.

#### Provisions for Posttrial Care

After completing the study, participants in the health awareness placebo and content placebo arms will receive the sugar video as postaccess to treatment.

#### Plans for Communicating Important Protocol Amendments to Relevant Parties

All relevant parties, including the ethics committee of the University of Heidelberg and the German Clinical Trials Register, will be notified about any modifications to the protocol that may impact the conduct of the study, the potential benefit of participants, or participant safety.

#### Dissemination Plans

We will disseminate the study findings through journal publications and conference presentations.

### Ethical Approval and Consent to Participate

Ethical approval was obtained from the Heidelberg University’s ethics committee (Universität Heidelberg Ethikkommission der Medizinische Fakultät) on March 18, 2020, protocol S-088/2020. All participants will undergo a process of informed consent. The consent form, which will be hosted on the Prolific platform, explains the purpose of the study, the risks and benefits of the research, and how a participant can contact a researcher (and/or the human subjects review board at Heidelberg University). By clicking the link, participants consent to participate in the study and are redirected to the Gorilla platform. The landing page contains additional information about the Gorilla platform. Participants can exercise their freedom to not participate at any point during the study (see Multimedia Appendix 1 for the informed consent form).

### Availability of Data and Materials

The data will be collected and stored on the Gorilla platform. The study investigators own and have complete control of the research data, which can be accessed at any time. For statistical analysis, the data will be downloaded and safely stored in a computing system maintained by the University of Heidelberg.

## Results

The study was approved by the Heidelberg University ethics committee on March 18, 2020 (S-088/2020). Participant recruitment and data collection were completed in December 2020. The data analysis was completed in April 2021, and the final results are planned to be published by August 2021.

## Discussion

### Principal Findings

There is growing evidence that entertainment-education media can be an effective strategy for promoting healthy behaviors [45-48]. However, further research is needed to understand which entertainment-education components can be modified to reduce reactance to health messages [3,49,50]. In this proposed study, we focus on a modifiable component—the perceived social authority of the health messenger—and its effect on reactance to a message about reducing sugar intake.

In recent years, video-based animation has emerged as a potentially powerful entertainment-education strategy for changing behavior [51-53]. This animation format has enabled the creative use of nonhuman and nonadult characters to promote more persuasive health messages [54]. We leveraged this animated format to create 3 culturally neutral characters that narrate a health message about sugar consumption. During the design phase, we assumed that a child narrator would be a more persuasive messenger because she would be perceived as nonthreatening or lacking a vested interest and therefore would be less likely to arouse reactance when compared with an adult narrator. However, we also considered that the child would not be taken seriously or that her lack of expertise would nullify the persuasiveness of the health message. We were unable to find prior research studies to inform our decision to use a child narrator. To this end, we propose an RCT to investigate whether reactance to the sugar message would be reduced if it was narrated by a preadolescent daughter, the daughter’s mother, or a family physician. Our results may show that a child can be a powerful and persuasive health promotion agent, which could inform future choices regarding the design and delivery of health messages.

### Strengths and Limitations

In a systematic review, Shen and Han [4] concluded that there is a lack of experimental methods to evaluate the effectiveness of entertainment-education media. They call for “controlled experiments to uncover the cognitive and/or affective factors that mediate entertainment-education’s effects” [4]. Our protocol responds to this call by leveraging experimental methods and carefully considering several factors that may mediate the role of social authority on reactance to the sugar reduction message, which we discuss below.

First, our study will use an RCT design to randomize participants to 1 of 3 sugar-intervention videos, a content placebo video, or a placebo video. The 3 intervention videos are exactly the same, except that the sugar message is narrated by the daughter, the daughter’s mother, or the family physician. The RCT should ensure that the enrollment stage does not introduce systematic differences between trial arms. For example, participants may have pre-existing health conditions, such as diabetes, which could affect their responses to the survey questions. However, random assignment will take care of this potential source of bias by distributing it uniformly across trial arms. Thus, holding all else equal, and because of randomization, differences in reactance toward the sugar message should be because of the experimental manipulation of the narrator’s social authority.

Second, the content placebo and placebo videos are an innovative feature of our study and will enable us to isolate the health awareness effect and content effect of the intervention video. The content effect can be quantified as the difference in mean state reactance (MSR) between the intervention arm and the content placebo arm. As both videos promote a health message, and because we will randomize, any significant difference in MSR should be because of the sugar reduction content of the intervention video. We can calculate the health awareness effect as the difference in MSR between the content placebo arm and placebo arm. As the content placebo video promotes a health message and the placebo video does not, the difference in MSR should be because of the health awareness generated by the sunscreen message. Thus, we can decompose the total intervention effect—the difference in MSR between the intervention and placebo arms—as the sum of health awareness and content effects. We are not aware of any previous entertainment-education study that has used an experimental approach to partition the effect of an intervention video in this way.

We do not believe that the differences between the placebo videos (which we did not create) and the sugar-intervention videos (which we created) will confound our results. Such differences may relate to the animation style, background shapes or colors, and target audience, among other design decisions. As mentioned, the main interest of our study is the difference in state reactance toward the sugar reduction message following random assignment to the 3 social authority levels. On the basis of the theoretical model described earlier, it is only the content of the message or the characteristics of the messenger that can threaten an individual’s freedom and arouse reactance. As the placebo video of earthquakes does not promote a health message, we expect it to arouse a very small (or even null) level of state reactance (the type of animation style of the placebo videos, for example, cannot realistically threaten an individual’s *freedom*). Therefore, the placebo video will provide a baseline measure of state reactance, which will enable us to quantify the content and health awareness effects. Further, we were very careful to select a content placebo video in which the messenger had culturally neutral or agnostic characteristics. In this case, the narrator of the sunscreen message is not seen, and it is not possible to determine his social authority. A possible exception is that the placebo videos are narrated by male voices and the sugar-intervention videos by female voices. However, it is unlikely that this design difference will be sufficiently large to bias our results significantly.

Third, we will conduct a list experiment in each of the 5 arms. This is the second experimental method that we leverage in our study design. We use a list experiment to reduce social desirability bias in participants’ responses to the behavioral intent questions about reducing sugar intake.It is likely that participants will already be primed to give socially acceptable responses to questions about their health and sugar consumption. The indirect questions (ie, how many statements do you agree with) provide protection to participants if they want to reject the sugar message without revealing this intention. To the best of our knowledge, few (if any) studies have used a list experiment approach to evaluate the effectiveness of an entertainment-education video to improve a given health outcome.

Finally, we will also use an experimental approach to measure participants’ engagement with the sugar videos. We will do this by *piggy-backing* this objective on the ethical requirement to give participants not randomized to the intervention the opportunity of watching the intervention video at the end of the study. Participants will be informed that they will not be compensated for their additional time, thus enabling us to estimate the proportion of participants who will voluntarily watch the sugar video and how long they watch the video. These findings will help us determine participants’ willingness to watch an entertainment-education video, especially when this willingness must be balanced against a time cost, as is generally the case in a real-world scenario.

